## Abstract

**Background:**

Physical activity is important to maintain health in older age, with physical activity in the outdoors providing mental and physical health benefits for all age groups. One way by which older people can engage in physical activity in the outdoors is through using suitable age-friendly outdoor exercise equipment, the Seniors Exercise Park. The ENJOY MAP for HEALTH aims to evaluate the effect of the Seniors Exercise Park installation and associated capacity building activities on park visitation, park-based physical activity by older people and delivery of community physical activity programs.

**Method:**

This study is a quasi-experimental (natural experiment) with pre and post study design evaluating the effect of age-friendly outdoor spaces with specialised outdoor exercise equipment on older people’s physical activity and wellbeing in six Victorian municipalities (local governments/councils). Each council will undergo four stages (site construction and development, promotion and marketing, capacity building and training, evaluation and sustainability). Several activities and methods will be employed from stage one through stage four to evaluate the potential impact of the age-friendly outdoor spaces on physical activity and wellbeing and will comprise the following elements: site observation and equipment utilisation, face to face intercept surveys, development of an online access monitor and community building activities.

**Discussion:**

The project is expected to result in a significant change in the physical outdoor environment for the participating councils and communities whereby older people and other community members will be able to engage in safe physical and social activity programs, socialise more and hence improve the overall wellbeing of older people.

**Trial registration:**

This trial is retrospectively registered with the Australian New Zealand Clinical Trials Registry. Trial registration number ACTRN12621000965808. Date registered 23/07/2021.

## Background

The pace of population ageing in Australia is increasing rapidly. In 2017, approximately 3.8 million people (15% of Australia’s total population) were aged 65 and over, by 2057, it is projected there will be 8.8 million older people in Australia (22% of the population) [1]. Older age is often characterized by the emergence of complex health issues affecting health and wellbeing. Low levels of physical activity contributes significantly to poor physical and mental health of older Australians [2]. Maintaining adequate levels of physical activity can reduce the risk of health problems in older adults [3]. However, older people have low participation rates in physical activity programs, with only 25% of Australians aged ≥ 65 meeting physical activity guidelines [4].

Exercising outdoors has various health benefits including mental and physical health for all age groups [5]. One way by which people can engage in physical activity in the outdoors is through using outdoor exercise equipment. Outdoor exercise equipment has become quite popular in recent years with many local governments (councils) installing it within local parks or recreational spaces within their municipalities [6–8]. The availability of outdoor exercise equipment offers an important environmental infrastructure to provide opportunities for physical activity and social connectedness in public settings at no cost for residents [6, 8]. Despite the emerging popularity of outdoor exercise equipment, limited suitable outdoor exercise equipment and space are specifically designed to suit older people [9]. Older people often experience complex health problems that limit mobility and functional movement which require careful consideration for the design and inclusion of suitable outdoor exercise equipment in recreational and leisure spaces.

We have been undertaking research for the past several years involving a specialised outdoor multimodal exercise equipment, the Seniors Exercise Park, and developed and tested an outdoor physical and social activity program for older people in the community. The Seniors Exercise Park integrates multimodal exercise stations that target balance (unstable/uneven surfaces), strength, flexibility and functional movements, designed for use by older people. Building on a Randomised Controlled Trial [10, 11], our work has expanded into public community settings involving the installation of the specialised equipment in multiple communities (The ENJOY project). Participation in the ENJOY program resulted in various health benefits including improved physical function and wellbeing as well as sustained engagement in physical activity, perceived enjoyment and enhanced socialisation for older people [12, 13].

The outcomes achieved so far from the ENJOY project suggest that the Seniors Exercise Park is effective in improving older people’s physical function and wellbeing and can be an important public health infrastructure investment in promoting physical activity for older people. It was also evident that working with local governments and community in partnership can play a major role in promoting community health through physical activity [14]. Wider implementation of this initiative to include more specialised equipment in the community and hence further local governments’ engagement can potentially have greater public health benefits. In addition, effective communication, strategic planning and community and older people engagement approaches are important for successful implementation [14]. The ENJOY MAP for HEALTH builds on our previous work and the lessons learnt to better improve the built environment to promote physical activity for older people. The ENJOY MAP for HEALTH aims to evaluate the impact of the Seniors Exercise Park installation and associated capacity building activities on older people’s park visitation, park-based physical activity and delivery of community physical activity programs. The ENJOY MAP for HEALTH will involve the installation of the specialised Seniors Exercise Park equipment supported by promotion and community capacity building activities in six municipalities in Victoria, Australia.

## Methods and design

All procedures involved in this trial will be conducted in compliance with the National Statement on Ethical Human Research and the Australian Code for the Responsible Conduct of Research. Ethical approval has been obtained from Monash University Human Research Ethics Committee, Melbourne Australia (Project ID: 25499). The study was designed according to the strengthening the reporting of observational studies in epidemiology (STROBE) statement [15].

The ENJOY MAP for HEALTH is a quasi-experimental (natural experiment) project involving the installation of specialised seniors exercise equipment supported by promotion and community capacity building activities in six municipalities in Victoria. The project comprises four stages in each of the six participating sites and is expected to be implemented in three blocks, with staggered commencement of two sites per block. Each block will involve the creation and activation of two age friendly sites (two municipalities). Each council will undergo four stages: site construction and development, promotion and marketing, capacity building and training, evaluation and sustainability, as shown in Fig. 1.

**Fig. 1 Fig1:**
[figure not shown]
Project’s stages for each site

To address the study aims, multiple methodologies will be employed throughout the project at each site (estimated 18 months process within each site) to evaluate the impact of site refurbishment and equipment installation on park visitation and physical activity engagement and participation of older people. These will include direct observations of park users, onsite intercept surveys with park users, online access monitor platform (using an online app, *ENJOY-ME-APP’*), and review of the physical activity program offered by the participating partners and or the respective local health/leisure providers. Please refer to Fig. 2 for the project’s timeline and activities.

**Fig. 2 Fig2:**
[figure not shown]
Study’s stages, activities, evaluation and timeline for each site

### Study setting and partners

In this project six councils will be involved, five in metropolitan Melbourne and one in regional Victoria as follows: Knox City Council (metropolitan), Banyule City Council (metropolitan), City of Ballarat (regional Victoria), Frankston City Council (metropolitan), City of Boroondara (metropolitan), and Bayside City Council (metropolitan).

The design of the project aims for implementation in staggered stages (in three blocks, two councils per block) where each council has nominated to undergo site refurbishment in a specific timeline based on council’s site upgrade plan. Each participating council will install the Seniors Exercise Park as part of a park/site upgrade (refurbishment) in the following block allocation:

Block one: Banyule City council (Ivanhoe Park, Ivanhoe) and City of Ballarat (Mt Pleasant Reserve, Mt Pleasant).

Block two – Bayside City Council (Thomas St Reserve, Hampton) and Knox City Council (Carrington Park, Knoxfield).

Block three – City of Boroondara (Victoria Park, Kew) and Frankston City Council (Wingham Park, Frankston).

Suitable locations have been chosen with some sites planned to undergo upgrade of play space for children in addition to the installation of the Seniors Exercise Park and other amenities (e.g., water fountain, shaded area, benches). As such there will be variation between sites around the overall site size, surrounding areas and amenities, and the additional play equipment.

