### Assessments

#### Outcome measures

##### Park observation and Seniors Exercise Park equipment usage

Observation of park and exercise equipment visitation and usage will take place prior to site construction (baseline) and at two time points: one month after the site is open for public and 12 months after baseline (Fig. 2). The inclusion of two measures post-refurbishment/construction allows time for residents to become aware of the new facilities [16]. The 12 months evaluation will take place at the same time of the year as the baseline assessments to account for potential seasonal effects.

Evaluation of usage and visitations will include periodic observation (using the System for Observing Play and Recreation in Communities (SOPARC)). The SOPARC is a reliable and feasible instrument for assessing physical activity and associated contextual data in community settings [17]. It is based on momentary time sampling techniques in which systematic and periodic scans of individuals and contextual factors within pre-determined target areas in parks are made. SOPARC was designed to obtain direct information on community park use, including relevant concurrent characteristics of parks and their users. It provides an assessment of park users’ physical activity levels, gender, activity modes/types, and estimated age and ethnicity groupings. Additionally, it provides information on individual park activity areas, such as their levels of accessibility, usability, supervision, and organization. As this study focuses on the usage of the Seniors Exercise Park, we will also collect additional data (not included in the original SOPARC protocol) by coding the interaction with the outdoor exercise equipment (i.e., ‘using equipment as intended’ or ‘playing/looking/sitting’ on the equipment) [18]. We will also note the number of people moving past the equipment area without interacting with the equipment. Each site will be divided into targeted areas to be scanned. Systematic scans will be conducted over a 7-day period (Monday-Sunday) with a total of 11 scans per day as follows (22 and 55 scans for weekend and weekdays respectively): every 30 min of all park visitors in the study area during early morning (07:00–08:30), mid-day (11:30–13:00) and late afternoon (16:00–18:30) [19].

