### Statistical methods

#### Sample size estimation for intercept surveys

To our knowledge, there are no natural experimental studies that have investigated the usage of exercise equipment following an installation and site activation of specialized outdoor exercise equipment for older people. Studies investigating park visitors before and after park refurbishment (including upgrade of play spaces for children) reported an increase of 33% in park visitors (all ages combined, with 17.3% age between 21–59, and 1.8% age 60 +), with an increase of 112% engagement in moderate physical activity by children and adults [26]. An observational study conducted in NSW reported only 3.8% (*n* = 112) of all visitors utilized outdoor exercise equipment for the purpose of exercise, among these approximately 5.3% (*n* = 6) were older people [18]. Another study reported only 15.6% of park users were older people (60–70 years), with people aged 60–70 being 60% less likely to report being regular park users than the younger age groups [27].

A previous study reported approximately 3 people/visitors every 1.5 h attending a community park [16]. With 3 periods of observations/ scans and total of 5.5 observation hours (early morning, mid-day, late afternoon) per day (estimated 12 people/visitors per day), we then estimate 84 visitors for the 7-day period. Based on a previous study, approximately 15.6–17.9% are expected to be older people [26, 27], hence a sample of 15 older people (17% of 84 visitors) will be expected to be recruited per site at the baseline observation period. With an estimated twofold increase in park visitors following site activation, a sample of 30 face to face intercept interviews will be targeted at the 12 month follow up observation period at each site. With potential 18–20% declining to participate (refusal), we will aim for a total of 38 intercept interviews (13 and 25 at baseline and follow up respectively, which accounts for potential refusals) per site with an overall sample of 228 interviewees across the six sites.

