#### A targeted outcome for ENJOY MAP for HEALTH project

A study investigating the impact of major renovations to playfields (mainly used for soccer and baseball) of two public parks as well as physical activity programming, reported a significant increase in visitation and overall physical activity (4-9 fold increase) compared to the controls [31]. This suggests that intervention that includes change in the physical built environment complemented with other community engagement is likely to result in substantial increase in physical activity participation. With limited studies reporting older people’s usage and engagement in physical activity, we estimate a twofold increase in visits by older people from baseline to the 12 months follow up at each site. Hence, we hypothesise that the intervention (Seniors Exercise Park installation and site activation) will result in *at least* twofold increase (100%) in the number of visitors (older people) between baseline to the 12 months follow up.

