#### Statistical analysis

Descriptive statistics will be used to report the overall park observation visitors, visitors’ characteristics, prevalence of usage of the Seniors Exercise Park, the type and level of physical activity of visitors (SOPARC). Descriptive statistics will also be used for the intercept surveys data to collate information about visitors’ perceptions about the park, motivation to use it, social connectedness/engagement with other at the park, their physical activity level and general wellbeing and their leisure/recreation activity at the park.

A generalised linear model [28] will be used to examine the effects of park refurbishment (equipment installation and site activation) on the total number of older people observed in the park, and the number of people walking and being physically active in the park. The statistical model will include terms for the intervention effect, the site effects, and seasonal effects; and overdispersion will be handled by using a quasipoisson family [32]. Statistical analyses will conducted using IMB SPSS Statistics version 26 (IBM Corporation, Armonk, NY, USA) and R [33].

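### The hypothesis credits the rise in older visitors to equipment installation and site activation, but some sites also upgrade a play space and the modelled ratio cannot separate the two

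*Protocol article*

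**What the plan says.** - **Hypothesis** (A targeted outcome for ENJOY MAP for HEALTH project): "we hypothesise that the intervention (Seniors Exercise Park installation and site activation) will result in" at least a doubling of older visitors. The expected size is given as "we estimate a twofold increase in visits by older people from baseline to the 12 months follow up at each site".
- **What is built** (Study setting and partners): the equipment goes in as one part of a wider site upgrade, with "some sites planned to undergo upgrade of play space for children in addition to the installation of the Seniors Exercise Park" and other amenities such as shade, benches and a water fountain. The section accepts that sites will differ in these respects. It does not say how many sites get a play-space upgrade.
- **Outcome and model** (Statistical analysis): effects are estimated "on the total number of older people observed in the park, and the number of people walking and being physically active in the park". A bracket there defines the refurbishment as equipment installation and site activation. The model terms are intervention, site and season, with a quasi-Poisson family. No comparison park is described.
- **Data that could separate the components** (Park observation and Seniors Exercise Park equipment usage): "Each site will be divided into targeted areas to be scanned", and interaction with the equipment is coded. Under Statistical analysis, use of the Seniors Exercise Park is assigned to descriptive reporting.
- **Broader wording elsewhere** (Methods and design): the text introducing the evaluation methods names site refurbishment as well as equipment installation as the thing evaluated.

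**The concern.** The cause named in the hypothesis is narrower than what changes at the sites, and the outcome is a whole-park count. Where a play space is upgraded in the same works, the before/after contrast at that site contains both changes. Site terms remove only differences that stay constant over time, so they do not remove a change that arrives together with the intervention.

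An adult aged 60 or over who comes because of the improved play space would thus count towards the effect credited to the exercise equipment and its activation. Councils deciding whether to buy this equipment could read the ratio as the return on the equipment programme when it is the return on a larger upgrade.

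**Working it through.** **1. The plan's own figure.** The protocol assumes a baseline mean of 15 older visitors per week.

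- Poisson CV = 1/√15 = 25.8%. Raised by half, 1.5 × 25.8% = 38.7%, as stated. This gives a negative binomial variance of (0.387 × 15)² ≈ 33.75.
- The stated power for a doubling was checked with 10,000 simulated data sets: six sites, mean 15 rising to 30, quasi-Poisson log-link model with site, intervention and season terms, two-sided 5% test. The seasonal swing of ±20% is an assumption.
- With the three planned observation points, power is 1.00 (Poisson) and 0.91 (negative binomial). This agrees with the protocol's claim of all data sets and over 80%. With baseline and 12 months only it is 0.99 and 0.76.

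The model as described is therefore understood. The question is what its intervention coefficient contains.

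**2. What the coefficient picks up.** Let the equipment and activation effect be zero. Suppose k of 6 sites have a play-space upgrade that raises older visits by a fraction r. With equal baseline means, the fitted ratio is approximately the mean of the site ratios:

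ratio ≈ 1 + (k/6) × r

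**3. Numbers for r = 0.33.** Under Sample size estimation for intercept surveys, the protocol cites earlier work that "reported an increase of 33% in park visitors". Using it for r is an assumption. The figure covers all ages, and it describes whole-park refurbishment that included play spaces, not a play space alone. The number of sites k is also assumed.

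| Sites with play-space upgrade | Ratio with no equipment effect | Share of a log twofold effect: ln(ratio)/ln 2 |
|---|---|---|
| 2 of 6 | 1 + 0.333 × 0.33 = 1.11 | 0.104/0.693 = 15% |
| 3 of 6 | 1 + 0.5 × 0.33 = 1.165 | 0.153/0.693 = 22% |
| 6 of 6 | 1.33 | 0.285/0.693 = 41% |

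The simulated ratios agree (1.11 to 1.12, 1.17 and 1.33).

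**4. The same point from the other side.** If the extra visits simply add, the rise that the equipment and activation must produce for the pooled ratio to reach 2.0 is 2 − (k/6) × 0.33. That is 1.89 for 2 sites, 1.84 for 3 and 1.67 for 6.

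**5. Effect on the test.** With no equipment effect, r = 0.33, three observation points and play space at 3 of 6 sites, the intervention term is significant in 10% (negative binomial) to 17% (Poisson) of data sets, against a nominal 5%. With 2 of 6 sites it is 7% to 10%.

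**The case against.** The strongest reply is that the protocol largely describes a whole-park upgrade already. Methods and design refers to site refurbishment. Study setting and partners says openly that play equipment and amenities will differ between sites. The Discussion speaks of upgrading outdoor space together with equipment and activities. Park visitation is a stated aim, so a whole-park count is a proper outcome. Even the hypothesis includes site activation, so it never credits the equipment alone. All of this stands, and it means the outcome should stay. It does not cure the hypothesis or the bracket under Statistical analysis, which leave the play space and amenities out of the named cause.

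A reader might also infer more than the documents support:

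- **That 41% of a doubling belongs to the play space, leaving 1.5-fold (2/1.33) for the equipment.** This needs all six sites to be affected, whereas the protocol says some. It also applies an all-ages figure to older people. The cited sentence gives 1.8% for age 60 and over, and it is unclear whether that is a share or a rise.
- **That the study could say nothing about the equipment.** The intercept survey asks about motivation to use the exercise park and, at 12 months, about equipment use and perceived changes to the park. QR scans record access by site, and observers code intended use. These give some evidence on attribution.
- **That a before/after model of equipment users would settle it.** The equipment does not exist at baseline, so intended use is zero by construction and a log-link ratio cannot be estimated. Descriptive reporting of use is reasonable.

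Finally, analyses by area and by site type are often left to an analysis plan, which is not at hand. The mismatch between the stated cause and the stated outcome is in the article itself.

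**Conclusion.** The point holds as a mismatch between the cause that is named and the quantity that is estimated. The hypothesis and the analysis bracket name installation and site activation. The estimated ratio is for everything that changed at the park, including a play-space upgrade at some sites. Followed as written, the plan would over-attribute the result, and its wording disagrees with the broader description under Methods and design.

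The size cannot be fixed from the documents. Under an assumed 33% rise in older visits at play-space sites, the contribution is a ratio of about 1.11 to 1.17 if two or three sites are affected, and 1.33 only if all six are. The documents do not show that older people will come for the play space, so this is a possible bias over an assumed range and not a demonstrated one.

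**What to change.** 1. **Wording.** In the hypothesis and in the bracket under Statistical analysis, describe the whole-park ratio as the effect of the full park upgrade plus site activation, consistent with Methods and design and Study setting and partners. State which sites have a play-space upgrade.
2. **Supporting analyses from the existing SOPARC target areas.** Report the same ratio with the play-space area excluded at all time points, and separately for sites with and without a play-space upgrade.
3. **Equipment use.** Report older people using the equipment as intended as post-installation counts, or as a share of older visitors, and not as a before/after ratio. Read this together with the intercept-survey and QR data when making statements about the equipment itself.

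The cost is a change of wording and some extra analysis of data already planned. With about 15 older visitors per site-week at baseline, counts by area or by site type will be small and intervals wide. Excluding the play-space area may also miss some older people who were drawn by the equipment but were in that area when scanned. These analyses should therefore support the whole-park result and not replace it.
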